## Abstract

**Background:**

LGBT patients may have unique psychosocial cancer care needs, and healthcare providers should have knowledge and understanding of these unique needs to effectively address disparities through the delivery of personalized healthcare. As such, our group developed and piloted a web-based LGBT cultural competency training designed specifically for oncologists called the Curriculum for Oncologists on LGBT populations to Optimize Relevance and Skills (COLORS). We designed a randomized pragmatic trial for oncologists to compare the effectiveness of the COLORS training versus a general online LGBT cultural competency training in improving LGBT-related knowledge, attitudes, and clinical practices.

**Methods/design:**

Study procedures include an 8-step approach for recruitment, randomization, retention, and completion of the interventions. Oncologists of any subspecialty who are currently practicing physicians will be identified from the American Medical Association Masterfile. Approximately 5000 oncologists will be sent a FedEx envelope with an invitation letter and study timeline. Electronic consent is obtained using a secure REDCap (Research Electronic Data Capture) portal hosted at the Moffitt Cancer Center (Tampa, FL) where the oncologists will complete the eligibility questionnaire, pre-training assessments, and then will be randomized to complete the COLORS training or an online general healthcare training offered by the National LGBT Health Education Center. Effectiveness of both trainings will be assessed utilizing self-reported measures of LGBT-related knowledge, attitudes, and affirming clinical practices. The measures will be collected before and directly after training completion, as well as 3-month post-training completion. The primary outcomes are changes in knowledge, attitudes, and practice behaviors regarding LGBT cancer patients from pre-test to post-test training in the COLORS training vs. the comparison training.

**Discussion:**

The overarching premise of this trial is to assess the effectiveness of the COLORS cultural competency training program. If successful, among oncologists who completed the COLORS training should yield statistically significantly improvements in knowledge, attitudes, and affirming practice.

## Background

The lesbian, gay, bisexual, and transgender (LGBT) community, also referred to as sexual and gender minorities, is a marginalized and medically underserved population. A growing body of evidence [1–12] demonstrates the LGBT population experiences increased risk for certain cancers, report lower satisfaction with cancer treatment, higher rates of psychological distress in survivorship, are less likely to engage in cancer early detection, and report higher rates of perceived discrimination in the health care setting. These findings suggest that LGBT patients may have unique psychosocial cancer care needs, and that healthcare providers should have knowledge and understanding of these unique needs to effectively address disparities through the delivery of personalized healthcare.

As cancer disparities in the LGBT community have largely been an ignored public health issue, consequently, there is a gap in LGBT-specific oncologist training. Despite advocacy for physician training in the unique needs of LGBT patients, there is a lack of widely adopted LGBT competency training opportunities tailored to practicing oncologists. In 2017, ASCO published guidelines [13] for oncology communities emphasizing the need for “Expanding and Promoting Cultural Competency Training and Incorporating Sexual and Gender Minority Training into Requirements and Certification Exams” and advocating for LGBT cultural competency training among oncologists specifically. Each of these recommendations acknowledge LGBT patients experience health outcomes which are directly related to the LGBT competency of their healthcare providers. For example, LGBT patients with cancer who are not comfortable discussing sexual orientation may be less likely to disclose their sexual orientation to their oncologist and are less likely to include their partner and/or family of choice in cancer care [14] which has the downstream impact of potentially increasing likelihood for poorer survivorship outcomes. Thus, these recommendations, taken together with the previous findings regarding LGBT cancer disparities, suggest oncologist education through targeted LBGT cultural competency training is crucial to improving the cancer care experiences of LGBT patients.

In 2017, our group published results [15] from a national sample of oncologists that showed oncologists have high interest in receiving LGBT health education yet have overall limited knowledge about LGBT health and cancer needs. This is problematic, as the number of people who identify as LGBT is growing, as are the number of cancer diagnoses in the USA. Based on conservative LGBT population estimates [16–18], there may be over 1 million LGBT cancer survivors living in the USA [19]. To address the interest in receiving LGBT health education and overall limited knowledge LGBT health and cancer needs, our group developed [20] and piloted [21] a web-based LGBT cultural competency training designed specifically for oncologists. Our preliminary findings [21] suggest the Curriculum for Oncologists on LGBT populations to Optimize Relevance and Skills (COLORS) training is feasible and acceptable among oncologists. Additionally, results from our pilot study showed improvements in LGBT-related knowledge and attitudes among oncologists who completed the training. Building on our formative pilot work, we designed a randomized pragmatic trial for oncologists to compare the effectiveness of the COLORS training versus a general (non-oncology focused) online LGBT cultural competency training in improving LGBT-related knowledge, attitudes, and clinical practices. Additionally, we will examine moderators of the effectiveness by potential modifiers such as age, race/ethnicity, sexual orientation and gender identity, practice setting, geographic region, and history of LGBT-related didactic training.

## Trial design

This study is a randomized pragmatic trial comparing the effectiveness of the COLORS training vs. a general healthcare (non-oncology) online LGBT cultural competency training among oncologists across the USA. Oncologists of any subspecialty who are currently practicing physicians and have not previously completed the COLORS training and/or the comparison training will be identified via the American Medical Association (AMA) Masterfile. Eligible oncologists will be randomized to complete the COLORS training or a standard online training via the National LGBT Health Education Center [22]. Effectiveness of the trainings will be assessed utilizing self-reported measures of LGBT-related knowledge, attitudes, and clinical practices. The measures will be collected before and directly after training completion, as well as 3-months post-training completion. The trial will analyze changes in LGBT-related knowledge, attitudes, and clinical practices pre- and post-training between the two study arms.

## Methods

### AMA Masterfile

The trial will identify practicing oncologists via the AMA Masterfile. The AMA Masterfile is a database of all practicing physicians in the USA independent of AMA membership or membership in any other elective organization. The AMA Masterfile is the only national database of licensed practicing physicians that does not require membership as medical students are entering into the database in the first year of school and remain in the database as long as they hold a medical license. The AMA Masterfile contains over 875,000 licensed physicians in the USA categorized by specialty and primary employment status (administrator, clinical practice, resident, etc.). All data in the Masterfile are obtained from primary sources only (medical schools, hospitals, medical societies, the National Board of Medical Examiners, state licensing agencies, etc.). The AMA Masterfile contains data on 100% of allopathic and 93% of osteopathic physicians and over 12,000 oncologists.

The trial will exclude oncologists whose primary position is listed as teaching, administrative, *locum tenen* or unclassified, as these individuals are less likely to provide clinical care to patients on a regular basis or at all. Additionally, oncologists from the state of Florida will be excluded since we conducted a pilot study [21] among oncologists at the Moffitt Cancer Center, University of Florida, and University of Miami. Residents and fellows will be excluded because they have less experience with patients and/or autonomy in determining practice protocol with patients. From a third-party vendor, the trial will obtain mailing addresses for 5000 oncologists with equal distributions across the nine US census divisions [23].

### Study procedures

Study procedures include an 8-step approach as summarized in Fig. 1, for recruitment, randomization, retention, and completion of the interventions.

**Fig. 1 Fig1:**
[figure not shown]
Study design and workflow to assess the effectiveness of a LGBT cultural competency training for oncologists

For step 1, approximately 5000 oncologists will be sent a FedEx envelope with an invitation letter and study timeline. The invitation includes a description of the study stating the research purpose, confidentiality of responses, the voluntary nature of the study will be explicitly stated, and a URL and QR code to enroll in the study. To increase the likelihood of response, the trial will use a modified Dillman three-wave method [24] and batched survey administration. The three-wave method includes the initial FedEx envelope and then two follow-up postcards (Table 1). Nine batches of invitations will be sent over a 14-week period with two follow-up postcards sent approximately 1 and 2 weeks, respectively, after the invitation letter. A follow-up email will also be sent among oncologists whose email addresses are available (*n* = 2,471).

**Table 1 Tab1:** Timeline for invitation letter and follow-up postcards

	Invitation letter by FedEx envelope (wave 1)	Follow-up postcard 1 (wave 2)	Follow-up postcard 2 (wave 3)	Email^**1**^
**Batch 1**				
**Group 1** (*N* = 495)	2/8/2021	2/12/2021	2/26/2021	3/26/2021^1^
**Group 2** (*N* = 495)	2/15/2021	2/19/2021	3/5/2021	
**Group 3** (*N* = 495)	2/22/2021	2/26/2021	3/12/2021	
**Group 4** (*N* = 522)	3/1/2021	3/5/2021	3/19/2021	
**Group 5** (*N* = 132)	3/15/2021	3/19/2021	4/2/2021	
**Batch 2**				
**Group 6** (*N* = 709)	4/19/2021	4/27/2021	5/7/2021	5/21/2021^1^
**Group 7** (*N* = 709)	4/26/2021	4/30/2021	5/14/2021	
**Group 8** (*N* = 709)	5/3/2021	5/7/2021	5/21/2021	
**Group 9** (*N* = 722)	5/10/2021	5/14/2021	5/28/2021	

Emails were available on 2471 of the 5000 oncologists and were sent out on two separate dates for each batch of participants

For step 2, oncologists will complete an eligibility screener questionnaire on a secure REDCap (Research Electronic Data Capture) portal hosted at the Moffitt Cancer Center (Tampa, FL). Practicing oncologists who are currently seeing patients will be included in the study. Individuals whose primary position is listed as teaching, administrative, *locum tenen*, or unclassified will be excluded. Additionally, residents/fellows and those who have already completed the COLORS training and/or the comparison training will be excluded.

### Informed consent

For step 3, after eligibility is confirmed, oncologists will be automatically directed to the informed consent REDCap page. The informed consent will include the contact information for the study coordinators, such that the participants may contact the coordinators with any questions prior to signing. Participants will provide their electronic signature for the informed consent.

### Study registration

For step 4, after informed consent is provided, oncologists will be directed to the registration page to provide an email address and demographic information including age, race/ethnicity, sexual orientation, gender identity, sex assigned at birth, and geographic region.

For step 5, oncologists will be directed to complete the pre-training study measures (described below), which include measures of LGBT-related knowledge, attitudes, and practices. In the pre-training assessment, data on medical degree (MD, DO, other, or prefer not to answer) as well as on whether the participants have friends or family that identify as part of the LGBT community will also be collected. Upon completion of the pre-training measures, participants will receive a link for a $10 Amazon gift card via email.

For step 6, after completing the pre-training measures, participants are block randomized across US census division to either COLORS training or the general LGBT competency training. Randomization will occur within 24 h of completion of pre-training measures. The REDCap randomization algorithm will be used to generate the randomization. Following randomization, study participants will receive an email with instruction on how to access and complete their training assignment, and they will be reminded to complete the training within 2 weeks. Participants will complete their assigned training at their own pace, as each website allows participants to return to where they left off.

### Post-training assessments

For step 7, after oncologists complete their assigned training, they will be directed to complete the post-training measures. In addition to measuring LGBT-related knowledge, attitudes, and clinical practices, post-training measures will also gauge the feasibility and acceptability of the training. Examples of feasibility and acceptability items include “Would you recommend this course to a colleague?”, “What barriers might you have that would interfere with implementation of new information learned from this training?”, and “How can this training be improved to better impact competence, performance and/or patient outcomes?”. Following the completion of post-training measures, participants will receive an email with a link for a $20 Amazon gift card and 2 CME of MOC credits provided by the New York University.

For step 8, the three-month post-training completion, participants will be emailed a link to complete a final round of study measures to examine longitudinal changes in knowledge, attitudes, and practices. Participants will receive another $40 Amazon gift card link after they complete the 3-month follow-up measures.

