### Study measures

The trial will assess effectiveness of the trainings in improving self-reported knowledge, attitudes, and clinical practice behavior using previously developed and established instruments [25–27]. Study measures will be collected at three time points: directly before the training (pre-training), directly after the training is completed (post-training), and 3-month following completion of the training.

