### Statistical analysis

The main outcomes are changes in knowledge, attitudes, and practice behaviors regarding LGBT cancer patients from pre-training to post-training assessment, as well as from pre-training to 3-month follow-up assessment (see knowledge, attitudes, and clinical practices measures listed above). We hypothesize that participants assigned to COLORS will demonstrate statistically significantly improvements in LGBT-related knowledge, attitudes, and clinical practices than participants assigned to the comparison training. Crude means with standard deviations and medians with interquartile ranges will be calculated for each measure at pre-training, post-training, and at 3-month follow-up within each study arm. Depending on the distributions of the measures, parametric or non-parametric methods, including repeated-measures analyses, will be used to test whether the measures significantly differ pre-training, post-training, and at 3-month follow-up within and between each study arm. The Holm-Bonferroni method will be used, as necessary, to adjust for multiple comparisons.

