### Power calculations

Power calculations are based on the primary objective of detecting statistically significant differences between the two study arms in pre- to post-training changes for the four measures listed above. The power calculations were based on the independent main effect of measure. Each measure is calculated as a single summary score and the power calculations are based on the assumption that approximately 12% of oncologists will agree to participate and be randomized (*n* = 600) and approximately 85% of those who are randomized (*n* = 255 per arm) will complete the post-training. Assuming 255 oncologists per arm will complete the training, a 2-sided alpha of 5%, and standard deviation (SD) of 1.0, power was calculated for expected ranges of mean summary scores/scales with potential deltas of the means (0.1 to 0.4) between both arms (Table 3). For all ranges of mean scores, when the detected delta of a mean is ≥ 0.3 between the 2 arms, we have substantial power to detect statistically significant differences, modest power when delta is 0.2, and low power when delta is 0.1. If the observed SD is 1.5, power drops to 0.852, 0.616, 0.324, and 0.100 for the respective deltas. However, with the expected large sample size, we estimate the SDs to be ≤ 1.0 as found in our previous work [21]. Additionally, power substantially improves across all scenarios if the delta of the means between both arms is ≥ 5 (*not shown*). Notably, the deltas used for the power calculations were based on previous studies, as the measures used in this study are not clinical measures and thus do not have clinically significant or clinically meaningful cutoff scores or thresholds.

**Table 3 Tab3:** Power calculations for the proposed scales and scores

Power for (score/scale)	Delta^a^	Mean score (control arm)	Mean score (COLORS arm)
0.994 (MHS)	0.4	12.1–12.5	12.5–12.9
0.994 (GAP)	0.4	55.1–55.5	55.5–55.9
0.922 (MHS)	0.3	12.1–12.5	12.4–12.8
0.922 (GAP)	0.3	55.1–55.5	55.4–55.8
0.615 (MHS)	0.2	12.1–12.5	12.3–12.7
0.615 (GAP)	0.2	55.1–55.5	55.7–55.7
0.203 (MHS)	0.1	12.1–12.5	12.2–12.6
0.203 (GAP)	0.1	55.1–55.5	55.2–55.6

^a^Delta of two means between both arms

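### Both follow-up assessments are defined by finishing the assigned training, and no assessment is described for randomised oncologists who do not finish

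*Protocol article*

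**What the plan says.** Under Study registration (step 6), "after completing the pre-training measures, participants are block randomized across US census division to either COLORS training or the general LGBT competency training". Access instructions follow, and "they will be reminded to complete the training within 2 weeks". The training is self-paced, so the two weeks are a reminder and not a cut-off.

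Under Post-training assessments, step 7 reads "after oncologists complete their assigned training, they will be directed to complete the post-training measures". Step 8 reads "the three-month post-training completion, participants will be emailed a link to complete a final round of study measures". The Study measures section defines the same two time points as "directly after the training is completed (post-training), and 3-month following completion of the training". The Abstract (Methods/design) and the Trial design section date them in the same way.

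Under Power calculations, about 12% of 5000 invited oncologists are expected to be randomised (600), and about 85% of those to complete. The calculation then proceeds "Assuming 255 oncologists per arm will complete the training". The Abstract's Discussion paragraph places success "among oncologists who completed the COLORS training".

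The Statistical analysis section words the hypothesis by assignment: "participants assigned to COLORS will demonstrate statistically significantly improvements". The Abstract and the Trial design section call the study a pragmatic trial of effectiveness.

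**The concern.** Finishing the course happens after randomisation and may depend on which course was assigned. If outcomes exist only for those who finish, the groups compared are no longer the groups that were randomised. One course is oncology-specific and the other general, and they run on different websites, so completion may well differ. The outcomes are knowledge, attitudes and affirming practice, and the oncologists who persist with such a course may be those who change most.

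A comparison among completers can then create or hide a difference. It also cannot show that a course which fewer oncologists finish achieves less in practice, which matters for a pragmatic effectiveness question. A later analysis plan can name an all-randomised analysis set, but it cannot supply outcomes that were never requested.

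**Working it through.** **1. Who has an outcome.** Inputs are from Power calculations: 5000 invited, 12% randomised, 85% completing.
- 5000 × 0.12 = 600 randomised, 300 per arm.
- 600 × 0.85 = 510, or 255 per arm.
- 600 − 510 = 90 without a post-training outcome, about 45 per arm if the loss is equal.

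**2. The plan's own power.** Two-sided 5%, SD 1.0, 255 per arm, normal approximation: power = Φ(δ / √(2/255) − 1.96), where √(2/255) = 0.0886. The opposite tail is negligible except at δ = 0.1, where it is included.

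| δ | Stated | Recomputed |
|---|---|---|
| 0.4 | 0.994 | 0.995 |
| 0.3 | 0.922 | 0.923 |
| 0.2 | 0.615 | 0.617 |
| 0.1 | 0.203 | 0.203 |

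The stated figures reproduce, so they rest on 255 completers per arm. The power arithmetic is not in question.

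**3. Bias of a comparison among completers.** In one arm let m be the share without an outcome and D the mean change of completers minus that of non-completers, in SD units. The mean over all randomised in that arm equals the completer mean minus m × D. With arm 1 COLORS and arm 0 the comparison training, the bias in the between-arm difference is m1 × D1 − m0 × D0. The article gives neither m by arm nor D, so every row below is an assumption (SD 1.0, 300 randomised per arm). Type I error is for a nominal two-sided 5% test.

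| m1 | m0 | D1 | D0 | Bias (SD) | Type I error |
|---|---|---|---|---|---|
| 0.15 | 0.15 | 0.5 | 0.5 | 0 | 5% |
| 0.15 | 0.15 | 0.5 | 0 | 0.075 | 13.5% |
| 0.20 | 0.10 | 0.5 | 0.5 | 0.05 | 8.7% |
| 0.10 | 0.20 | 0.5 | 0.5 | −0.05 | 8.7% |
| 0.20 | 0.10 | 1.0 | 0 | 0.20 | 62% |

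The first row shows that missing outcomes alone do not produce bias. The third and fourth rows show that the sign depends on which arm loses more.

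**4. The same question as a correlation.** Let p be an arm's completion rate and r the correlation between propensity to complete and the change score. Under a normal model, the completer mean is raised by r × φ(z)/p, where z is the normal quantile at p.
- p = 0.90: 0.1755 / 0.90 = 0.195.
- p = 0.80: 0.2800 / 0.80 = 0.350.
- Difference: 0.155. At r = 0.3 the bias is 0.046 SD; at r = 0.5 it is 0.077 SD.

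The implied completer/non-completer gap is r × φ(z) / [p(1 − p)]. At r = 0.3 this is 0.59 SD (p = 0.90) and 0.52 SD (p = 0.80). At r = 0.5 it is 0.98 and 0.88 SD. These gaps are not small, and the reader can judge how likely they are.

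**5. Power if all 300 per arm are assessed.** √(2/300) = 0.0816.
- Effect undiluted, δ = 0.3: power 0.957.
- The 15% who do not finish gain nothing (assumption), so δ = 0.3 × 0.85 = 0.255: power 0.878. For δ = 0.2 × 0.85 = 0.17 it is 0.549.

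**The case against.** A reader might infer that non-completers are barred from assessment, that the analysis set is completers only, and that the protection of randomisation is therefore lost. The article supports none of these as fact.

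No sentence excludes non-finishers from the measures. Step 8 is addressed to participants without further restriction, Fig. 1 is not shown, and the full protocol may say how stalled participants are handled. No analysis set is named. The hypothesis is worded by assignment, and repeated-measures methods are allowed. Powering on the expected 85% is a routine attrition allowance, and the Abstract's phrase about completers is a broken sentence whose counterpart in the main Discussion carries no such restriction. All of this stands. What remains is that every description of the two time points uses completion as its reference, so followed as written, neither has a date for someone who never finishes. A repeated-measures model could keep such a person's baseline score, but that person adds no post-baseline information and the result leans on a missing-at-random assumption.

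The objection on size also stands in part. The outcome is change from a baseline taken before randomisation. If propensity to complete correlates equally with the scores before and after training, and their SDs are equal, the correlation cancels in the change score and the bias is zero. A link between attitudes and completion is therefore not enough; the link must be with the change itself. With a positive correlation, the arm with lower completion has the more inflated mean. If the oncology-specific course is finished more often, this bias works against COLORS, so false superiority should not be presumed.

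Finally, moving everyone's first follow-up to a fixed date would catch some people mid-course, and step 7 also carries the course-evaluation items and educational credit. The fix below respects that.

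**Conclusion.** The point holds as a gap in data collection. As written, about 90 of 600 randomised oncologists would have no outcome, while the hypothesis concerns assigned arms. That figure rests only on the plan's 12% and 85%, and the split of about 45 per arm assumes equal loss.

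Bias is a risk of unknown size and direction. It is zero if the missing share and the completer/non-completer gap in change scores are alike in both arms. Under the assumed 90% against 80% completion and a correlation of 0.3 to 0.5 with the change score, it is about 0.05 to 0.08 SD. Table 3 spans deltas of 0.1 to 0.4 and names no single target, so this ranges from a small part of the largest delta (0.046 / 0.4 = 12%) to most of the smallest (0.077 / 0.1 = 77%).

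**What to change.** **Data collection.** Keep the immediate post-training assessment for those who finish. For those who have not finished by a set time after randomisation, send the knowledge, attitude and practice measures then, without the course-evaluation items or the educational credit. Send the final assessment to every randomised oncologist at a set time from randomisation.

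**Analysis.** State that the primary comparison is by assigned arm among all randomised, report completion by arm, and keep the completer comparison as secondary.

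**If data collection has closed,** as the Trial status section indicates, analyse all randomised by assigned arm using baseline scores, add a missing-not-at-random sensitivity analysis, and limit the between-arm conclusion accordingly. Outcomes not collected cannot be recovered.

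**Cost.** Some extra gift cards, a change to the survey invitations, and less uniform timing between finishers and non-finishers. The effect may be diluted: if non-completers gain nothing, power at delta 0.3 is about 0.88 with 300 per arm, against the stated 0.922. That figure assumes all 300 respond; with fewer responses it would be lower.
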